#### Supervision for case management

To standardize the intensity and quality of EIS, we will conduct training courses at least twice a year with required participation by case managers at each site, at which they will have to discuss their practices and cases. Supervision in meetings will be provided, and professionals and supervisors of other services will discuss and provide advice about their practices and cases.

### Outcomes and measurement items

We will adopt the function domain of the global assessment of functioning (GAF-F) [25] scores at the first end point as the primary outcome measure. Secondary outcomes will be GAF-F at the second and last end points, symptom domain of global assessment of functioning (GAF-S), PANSS,[12] the World Health Organization quality of life 26-item version (WHO-QOL26),[26,27] brief evaluation of medication influences and beliefs (BEMIB),[28] care satisfaction of participants and their families, educational and vocational recovery rates, remission rate, re-admission rate, lost to follow-up rate, self-harm and suicide attempt rate, suicide rate, engagement behavior, and direct and indirect costs at each end point. All measurement items will also be assessed at baseline. We will record the presence of comorbid mental and physical disorders and relevant sociodemographic and clinical information about the participants and their families at baseline and at each end point. The details of the assessments are discussed in the following sections.

#### GAF, GAF-F, and GAF-S

GAF records the current objective symptomatic and functional conditions of participants on one analogous scale ranging from 0 (poor) to 100 (good)[25]. GAF-F rates the social and occupational functions of patients, and GAF-S rates their symptoms. GAF is adopted as the worse score of GAF-F and GAF-S. We will also use the modified GAF scale [29] to measure GAF, GAF-F, and GAF-S.

#### PANSS

PANSS records the current objective symptoms of patients on 30 items[12]. PANSS consists of 3 domains: positive symptoms, negative symptoms, and general psychopathology. Each item is rated from 1 (absent) to 7 (extreme), and the total score ranges from 30 to 210.

#### WHO-QOL26

WHO-QOL26 [26,27] measures the current subjective satisfaction of participants regarding their quality of life on 26 items. WHO-QOL26 consists of 4 domains: physical health, psychological health, social relationships, and environment. Each item is rated from 1 (poor) to 5 (good) and presented as an average score.

#### BEMIB

BEMIB measures the current drug adherence of participants to their medications on 8 items[28]. Each item is rated from 1 (completely disagree) to 5 (completely agree), and the total score ranges from 8 to 40.

#### Care satisfaction

Care satisfaction will be measured by one simple item rated from 1 (very satisfied) to 4 (very dissatisfied). Participants and their families will provide subjective care satisfaction ratings after enrollment.

#### Recovery rate

Recovery will be measured by using the definition sheet adopted for EIS in England[30]. The item in the sheet termed "TRAINING AND OCCUPATION," which is rated from 0 (employment) to 4 (Not in Education, Employment or Training; NEET), will be assessed. For the initial assessment, this rating will be taken from the best occupational status achieved within the last 6 months for each end point taken from the point of last assessment.

#### Remission rate

We defined remission using a proposal from the Remission in Schizophrenia Working Group [31] that defined symptomatic remission of illness using 8 corresponding PANSS subscores (P1, P2, P3, N1, N4, N6, G5, and G9) of mild or less simultaneously on all items and for which remission regarding these scores was maintained for at least 6 months.

#### Re-admission rate

We will record all voluntary and involuntary admissions of participants at registration and during the follow-up period.

#### Lost to follow-up rate

Lost to follow-up will be defined at each end point as the refusal of further treatment despite the need and several attempts of reengagement (phone calls to patients and families in both groups and home visits to participants in the CAP group)[32]. We will consider the last successful contact the date of lost to follow-up.

#### Self-harm, suicide attempt, and suicide rate

Self-harm and suicide attempt will be measured using the items in the definition sheet "SELF-HARM and SUICIDE" on a scale of 0 (None) to 4 (Severe problems)[30]. We will assess the inquiry sheets for all of the suicide and severe self-harm actions at all sites.

#### Engagement behavior

Engagement, family engagement, and social relationships will be measured using the items in the definition sheet "ENGAGEMENT, FAMILY/CARER ENGAGEMENT, and RELATIONSHIPS" on a scale of 0 (Severe problems) to 4 (Very good) [30].

#### Service costs and cost-effectiveness

Service costs will be calculated using the Client Service Receipt Inventory (CSRI),[9,33], which can estimate service costs and cost-effectiveness, particularly in psychiatric contexts. On the basis of the CSRI, we will conduct interviews of daily living (e.g., service use, school, employment, and family conditions) at registration, at each end point, and if possible, at intermediate points between end points. Service costs will be calculated by the service costs and appropriate local unit costs. Cost-effectiveness will be calculated by the combination of the outcomes related to the service costs and participant subjective quality of life assessments using WHO-QOL26. Unavailable cost data will be estimated using other resources and models.

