## Methods

### Trial design

This trial is designed with effectiveness, interventional, parallel, single-blinded (open but blinded raters) trial. The allocation of participants will be equal (1:1) between the comprehensive approach (CAP) and standard care (SC) groups. The entire trial design is illustrated in Figure 1. After enrollment, all participants will be provided standard care, and in the CAP group, comprehensive community-based care by an early intervention team will be provided for 18 months. Eighteen months after enrollment, all participants will be provided standard care only. The assessment of clinical data will be conducted at enrollment and 18 (first end point), 36 (second end point), and 60 months after enrollment (last end point). The target sample size will be 150, and registration will occur from March 1, 2011, to September 30, 2012. The last follow-up date will be September 30, 2017. This trial was registered in the University Hospital Medical Information Network Clinical Trials Registry (UMIN-CTR) accepted from the International Committee of Medical Journal Editors (ICMJE) (No. UMIN000005092).

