### Data reliability

Some methodological problems regarding interrater reliability will exist. To control the quality of data assessment, we will conduct lectures for PANSS and GAF, including GAF-F and GAF-S, more than once a year using video movies to ensure accurate scoring. We will also calculate interrater reliability for PANSS and GAF scores provided by the raters in the lecture, and we will provide feedback for these results to maintain a high quality of assessment.

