### Randomization

Enrollment and random allocation will be performed by central registration at the University Hospital Clinical Trial Alliance Clinical Research Supporting System (UHCT ACReSS) at the University of Tokyo. The managers of each site will enroll participants after examining their eligibility and informed consent. The type of allocation will be stratified and block randomization. We will adopt stratification as sites and inpatients/outpatients at enrollment. Owing to allocation concealment, the block size will be provided by UHCT ACReSS and will not be revealed to any researchers or staff until the end of the enrollment period. As this is a single-blinded trial, all assessments after enrollment will be conducted by independent raters with no knowledge of any treatment and care provided this trial.

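### The statement that every follow-up assessment is made by blinded raters cannot hold for the scheduled service-use interview, and nothing stated keeps that interview away from the GAF-F rater

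*Protocol article*

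**What the plan says.** The Trial design section describes a "single-blinded (open but blinded raters) trial". Under Randomization, the article states that "all assessments after enrollment will be conducted by independent raters with no knowledge of any treatment and care provided this trial".

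Under Service costs and cost-effectiveness, a Client Service Receipt Inventory (CSRI) interview is planned: "we will conduct interviews of daily living (e.g., service use, school, employment, and family conditions) at registration, at each end point". The same sentence adds intermediate interviews between end points where possible. Outcomes and measurement items lists "engagement behavior, and direct and indirect costs at each end point" among the secondary outcomes, so this interview supplies trial outcome data at 18, 36 and 60 months.

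The primary outcome is the GAF function score (GAF-F) at 18 months. Data reliability confirms that it is scored by raters: "We will also calculate interrater reliability for PANSS and GAF scores provided by the raters in the lecture".

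The arms differ in services received. Under Trial design, "in the CAP group, comprehensive community-based care by an early intervention team will be provided for 18 months". The Intervention section gives the standard care (SC) group standard care only.

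**The concern.** A person who asks a participant which services they have used will normally hear about case managers and an early intervention team if the participant is in CAP, and will not if the participant is in SC. That person then knows what care was given. Yet the blinding statement covers all assessments after enrolment, and costs are an outcome assessed after enrolment.

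What is at stake is the only blind in the trial. Participants and treating staff know the allocation, and GAF-F is a single judgement on a 0 to 100 scale. If the person making that judgement has already heard the service history, at that visit or at an intermediate interview before 18 months, the protection is lost for that rating. The 36- and 60-month GAF-F scores, which are secondary outcomes, are exposed too if the same rater returns with that knowledge.

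**Working it through.** The plan gives no figure on this point to reproduce. The check is mainly a comparison of statements.

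**Statements side by side**

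1. Randomization: all assessments after enrolment are made by raters unaware of care.
2. Outcomes and measurement items, with Service costs: a service-use interview feeds an outcome at each end point, and intermediate interviews may be added.
3. Trial design and Intervention: until 18 months, early intervention team contacts occur in CAP only.
4. From 2 and 3, whoever takes the interview at or before 18 months will usually learn the arm.
5. From 1, that person is supposed to be a rater who does not know it. Statements 1 and 2 therefore conflict for this interview.
6. The article does not exempt the interview from statement 1, assign it to a different person, or place it after the GAF-F rating.

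After 18 months both arms receive standard care only. A later interview about recent services is therefore less revealing in itself. The risk at 36 and 60 months comes mainly from what a returning rater learned earlier.

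**Illustration of what a rater shift would do (assumed; the document gives neither a GAF-F standard deviation nor a bias size)**

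Inputs from the document: 150 participants allocated 1:1, so 150/2 = 75 per arm; Student's t test; alpha 0.05, taken here as two-sided. Assumptions: no true effect, and an average shift of b SD in favour of CAP.

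Noncentrality = b × √(75/2) = 6.12 × b, with 75 + 75 − 2 = 148 degrees of freedom.

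| Assumed shift b (SD) | Noncentrality | Two-sided false-positive rate |
|---|---|---|
| 0 | 0 | 5.0% |
| 0.05 | 0.31 | 6.1% |
| 0.10 | 0.61 | 9.3% |
| 0.20 | 1.22 | 22.9% |
| 0.30 | 1.84 | about 45% |

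To put b on the GAF-F scale, suppose a shift of 2 to 3 points. With an SD of 15 this is 2/15 = 0.13 to 3/15 = 0.20 SD. With an SD between 10 and 20 the range is 2/20 = 0.10 to 3/10 = 0.30 SD. For comparison, the Sample size section cites an effect of 0.26 for GAF-F from the Dutch trial; 0.13/0.26 and 0.20/0.26 are about one half and three quarters of it (51% and 77% before rounding the shift).

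The shift is an average over the arm. If only half of the CAP ratings were affected by 0.20 SD, b would be 0.5 × 0.20 = 0.10 and the rate about 9.3%.

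**The case against.** The strongest reply is that the key fact is absent: the article never says that the GAF-F rater conducts the service-use interview, nor in what order. Who completes which form is operational detail that a journal article commonly leaves to the full protocol. This stands against any claim that the blind on GAF-F is broken. It does not answer the narrower point, because the article makes a universal statement that its own schedule contradicts. If the full protocol separates the roles, the statement is still wrong as written.

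A second reply is that the blinding statement was never meant literally. Care satisfaction comes from participants and families, quality of life is subjective, admissions are recorded, and the only instruments tied explicitly to raters are PANSS and GAF. That is a reasonable guess at the intent, and it is why the remedy includes rewording. But the text says all assessments, and a site following it literally would have the blinded rater take the service history.

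A reader might also infer that the engagement and care satisfaction items break the blind. The document does not support this. Satisfaction is self-reported on one item. Engagement is a 0 to 4 score applied in both arms, and nothing shows that scoring it reveals the arm. The case rests on the service-use interview.

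Finally, the size of any bias is pure assumption. That is correct.

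**Conclusion.** The blinding statement and the service-use interview cannot both hold for the person who takes that interview. This is a misstatement of a design property, and the stated procedures do not prevent the rater of the primary outcome from learning the arm. It should be corrected.

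A reader might infer that GAF-F at 18 months will be rated unblinded, or that a known part of any observed effect would be rater bias. Neither follows. The document is silent on who interviews and in what order, so bias in GAF-F is a risk and not a certainty. The error rates of 6.1% to about 45% for shifts of 0.05 to 0.30 SD show only how sensitive the t test would be with 75 per arm. They rest on an assumed shift, an assumed GAF-F standard deviation where points are quoted, and no true effect.

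**What to change.** 1. At every end point, rate and lock GAF-F, GAF-S and PANSS before any service-use item is opened.
2. Have the CSRI interview, at end points and at intermediate points, taken by existing site staff who do not rate outcomes. Form order alone would protect the 18-month rating but not those at 36 and 60 months if the same rater returned.
3. Reword the blinding statement under Randomization to exempt only the CSRI service-use interview and self-reported or record-based items. Keep the blind for all other rater-scored outcomes, including the self-harm and suicide attempt scale, which feeds the interim stopping rule, and the occupational recovery scale.
4. Record the rater's guess of arm immediately after the GAF-F rating, so that the success of the blind can be reported.

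The cost is some coordination of staff and form order, one added field and a revised sentence. A small downside is that service-use answers cannot inform the GAF-F rating. Sample size, analysis and care are unchanged.

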### Data reliability

Some methodological problems regarding interrater reliability will exist. To control the quality of data assessment, we will conduct lectures for PANSS and GAF, including GAF-F and GAF-S, more than once a year using video movies to ensure accurate scoring. We will also calculate interrater reliability for PANSS and GAF scores provided by the raters in the lecture, and we will provide feedback for these results to maintain a high quality of assessment.

### Sample size

The planned number of participants is 150, as determined by previous RCT results, the clustering effects of each site, and the possibility of exhaustion of our resources. An RCT of EIS for patients with FEP in Holland indicated that EIS improved participant GAF-F scores in 24 months[5]. Another RCT of CBT in England revealed that CBT improved patient readmission rates and GAF scores in 18 months[6,7]. The effect sizes calculated from their results were 0.26, 0.46, and 0.58, respectively. The estimated sample sizes using G*Power 3[34] (alpha error = 0.05, beta error = 0.2) were 370, 150, and 96, respectively.

We will adopt 1 interim analysis and consider stopping the trial if the participants in the CAP group have unexpected effective outcomes compared with those in the SC group. We will conduct the interim analysis when half of the participants finish the trials until the first end point. Stopping rules will be planned on the basis of the O'Brien-Fleming method [35] for the GAF-F score, re-admission rate, lost to follow-up rate, self-harm and suicide attempt rate, and suicide rate at the first end point. We will consider stopping the trial on the basis of the stopping rule, baseline data, missing data, and site. Because of ethical issues, we will provide EIS to all participants until 18 months after allocation if the trial is halted.

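### The planned 150 matches the calculation for a readmission effect (0.46); under the only GAF-F effect cited (0.26) power is about 35% to 48%, and the 370 printed for that effect is not on the same basis as the 150

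*Protocol article*

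**What the plan says.** All references are to the Protocol article.

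- **Planned size (Sample size section):** "The planned number of participants is 150, as determined by previous RCT results, the clustering effects of each site, and the possibility of exhaustion of" the team's resources.
- **Earlier results (Sample size):** an early intervention trial in Holland "indicated that EIS improved participant GAF-F scores in 24 months". A second trial, in England, "revealed that CBT improved patient readmission rates and GAF scores in 18 months".
- **Effects (Sample size):** "The effect sizes calculated from their results were 0.26, 0.46, and 0.58, respectively".
- **Totals (Sample size):** calculated with "alpha error = 0.05, beta error = 0.2) were 370, 150, and 96, respectively". Sidedness is not stated.
- **Primary outcome (Outcomes and measurement items):** GAF-F "scores at the first end point as the primary outcome measure", that is, at 18 months. The re-admission rate is among the secondary outcomes.
- **Primary test (Statistical method):** Student's t test.
- **Allocation (Trial design):** "The allocation of participants will be equal (1:1) between the comprehensive approach (CAP) and standard care (SC) groups", so 75 per arm.
- **Discussion:** names sample size as a possible limitation, without a power figure.

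**The concern.** Read in order, the three results, effects and totals pair up as GAF-F with 0.26 and 370, readmission with 0.46 and 150, and GAF with 0.58 and 96. The adopted total therefore equals the one for readmission, although the trial will be judged on GAF-F. The plan gives no reason why a readmission effect from a CBT trial should size a comparison of mean GAF-F.

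The only error rates printed are an alpha of 0.05 and a beta of 0.2, and the planned number coincides with one of the three totals computed from them. A reader may come away thinking that the primary comparison carries those error rates. If the true effect is near the one GAF-F figure cited, the primary test would more likely miss it than find it, and a non-significant result could be given more weight than it can bear when it is used, as the Discussion intends, to inform policy.

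The three totals also do not appear to come from one calculation. That matters because the 370 is the plan's only indication of how far 150 falls short for GAF-F.

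**Working it through.** **Inputs.** Effects d = 0.26, 0.46, 0.58; totals 370, 150, 96; alpha 0.05; power 0.80 (Sample size). Allocation 1:1 (Trial design), so n = 75 per arm. Student's t test (Statistical method).

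**Step 1: reproduce the plan's totals.** Normal approximation, per arm: n = 2(z_alpha + z_beta)²/d², rounded up and doubled. Two-sided, (1.960 + 0.842)² = 7.849; one-sided, (1.645 + 0.842)² = 6.183.

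- d = 0.46, two-sided: 2 × 7.849/0.2116 = 74.2, so 75 per arm, total 150.
- d = 0.26, two-sided: 2 × 7.849/0.0676 = 232.2, so 233 per arm, total 466.
- d = 0.26, one-sided: 2 × 6.183/0.0676 = 182.9, so 183 per arm, total 366.

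The noncentral t calculation gives nearly the same totals:

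| d | Plan | Two-sided: normal / t | One-sided: normal / t |
|---|---|---|---|
| 0.26 | 370 | 466 / 468 | 366 / 368 |
| 0.46 | 150 | 150 / 152 | 118 / 120 |
| 0.58 | 96 | 94 / 96 | 74 / 76 |

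So 150 and 96 reproduce two-sided only, and 370 reproduces one-sided only. Rounding of the effect does not explain this: for d from 0.255 to 0.265 the two-sided t total runs from 486 down to 450. With 370 patients, two-sided power at d = 0.26 is 70%, not 80%.

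**Step 2: power of the primary test at 75 per arm.** Noncentrality = d × √(n/2) = d × √37.5 = 6.124d, with 148 degrees of freedom. For d = 0.26 this is 1.592; the normal approximation gives Φ(1.592 − 1.960) = Φ(−0.368) = 35.7%, and the noncentral t gives 35.3%.

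| d | Two-sided 0.05 | One-sided 0.05 |
|---|---|---|
| 0.26 | 35.3% | 47.6% |
| 0.46 | 79.9% | 87.7% |
| 0.58 | 94.2% | 97.1% |

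**Step 3: other readings of the GAF-F line.**

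- If 370 is the correct two-sided total and 0.26 is the slip, the implied effect is d = 0.292, and power at 75 per arm is 42.7%.
- If 0.26 is a rounded value between 0.255 and 0.265, two-sided power is 34.2% to 36.4%.

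**Step 4: what 150 can detect.** The smallest effect with 80% power is 0.46 SD two-sided (0.41 one-sided). The two-sided value is 0.46/0.26 = 1.8 times the cited GAF-F effect.

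**Step 5: allowances.** Since 150 equals the unadjusted two-sided total for 0.46, it shows no addition for dropout, site clustering or the interim analysis. The article gives no dropout rate. Assuming 10%, 20% or 30% (67, 60 or 52 per arm), two-sided power at d = 0.26 falls to about 32%, 29% or 26%.

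**The case against.** The strongest defence is that the plan makes no claim that is contradicted. It nowhere says that 150 gives 80% power for GAF-F. It prints the 370 beside the 150, gives three reasons for its choice (prior results, clustering, resources), and concedes sample size as a limitation. This stands. A reader might infer that the authors promised 80% power on the primary outcome and misreported it; the text does not support that.

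Second, 0.26 is a benchmark and not this trial's assumption. It comes from Holland at 24 months, whereas the primary end point here is at 18 months. The Discussion says that earlier results depend on the care given to controls and that community services are scarce in Japan. It says so about persistence of effect, but the same reasoning could favour a larger contrast here. The 18-month GAF benchmark of 0.58 would give 94% power. This stands in part: power is about 35% only if the 0.26 applies, so a flat statement that the trial has 35% power would go too far. However, the 0.58 is for overall GAF, which the section on GAF, GAF-F and GAF-S defines as the worse of the function and symptom scores. It is a related but different measure, and the plan offers no argument for using it, or the 0.46, in place of the GAF-F figure.

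Third, limited resources can justify 150. They can, but they do not change what 150 delivers. It would equally go beyond the text to say that resources alone set the number.

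**Conclusion.** The concern holds in a conditional form. The adopted 150 matches the readmission calculation, and under the only GAF-F effect that the plan cites, the beta of 0.2 is not met for the primary outcome. Power is about 35% two-sided, about 43% if 370 is right and the effect is nearer 0.29, and about 48% if the test is one-sided. The range reflects the unstated sidedness and the mismatch between 0.26 and 370; no reading comes near 80%. These figures assume 75 analysed per arm and no loss for dropout, clustering or the interim look.

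Separately, the 370 is inconsistent with the 150 and 96: on their two-sided basis, 0.26 needs about 468. The shortfall against the GAF-F benchmark is then about threefold (468/150 = 3.1) and not the 2.5-fold that the printed 370 suggests (370/150 = 2.5).

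The result rests on pairing the lists in the order given. Even if the two results of the English trial were swapped, the 150 would belong to overall GAF and still not to GAF-F.

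**What to change.** Keep 150 and revise the Sample size section:

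1. State whether the test is one-sided or two-sided, and put all three totals on that basis. If two-sided, change 370 to about 468, or correct the 0.26 if that is the slip.
2. State what the sample delivers for the primary outcome. Suggested wording: *With 75 per arm and a two-sided alpha of 0.05, the trial has 80% power for a GAF-F difference of 0.46 SD, before any allowance for dropout, clustering or the interim analysis, and about 35% if the 0.26 SD of the earlier GAF-F trial applies.*
3. Say that 150 was chosen from prior results, site clustering and resource limits, and not from the GAF-F benchmark.
4. Say that the primary result will be interpreted by the difference in GAF-F and its 95% confidence interval, so that a non-significant result is not read as evidence of no effect.

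This is rewording only: no extra patients, and no change to the outcome or the test. The cost is that the stated power becomes less favourable.

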#### Pharmacological therapy in accordance with the guidelines for FEP

Several pharmacological guidelines for schizophrenia and mood disorder are available worldwide. However, some psychiatrists in Japan have developed experimence-oriented strategies that result in polypharmacy for patients with schizophrenia[22]. Polypharmacy can exacerbate the negative symptoms and cognitive impairments of patients in addition to promoting dropped-out from treatment[22]. One reason why psychiatrists tend to prescribe more tablets may be that patients' treatment strategy and prescription are mainly decided by their psychiatrists who know little information except from the consultation with patients and their family members. In this trial, we will conduct regular meetings with early intervention teams and propose treatment and prescription strategies to psychiatrists according to the guidelines to eliminate unnecessary prescriptions.

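### Suicide and self-harm sit under a stopping rule that only CAP benefit can trigger, at one late look, and for suicide the boundary is practically out of reach

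*Protocol article*

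**What the plan says.** The rule is in the Protocol article under Sample size. There is one interim analysis, made when half of the participants have reached the first end point at 18 months. The sponsor will "consider stopping the trial if the participants in the CAP group have unexpected effective outcomes compared with those in the SC group". O'Brien-Fleming rules are to be planned "for the GAF-F score, re-admission rate, lost to follow-up rate, self-harm and suicide attempt rate, and suicide rate at the first end point". The decision will also take account of baseline data, missing data and site. If the trial is halted, all participants are to receive EIS until 18 months after allocation. No numerical boundary is given, and it is not said whether the test is one- or two-sided.

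Under the heading on self-harm, suicide attempt and suicide rate, inquiry sheets for every suicide and severe self-harm event will be assessed at all sites. No threshold is attached to them, and no link to the stopping rule is stated.

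**The concern.** Two of the five outcomes under the rule are the trial's gravest safety events. The trigger is good results in CAP, and the action on halting extends the service to everyone. That action makes sense after a benefit stop; after an excess of suicides or self-harm in CAP it would do the opposite of what a monitor would want. The rule therefore lists safety outcomes without being able to respond to harm in the intervention arm.

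Two further features weaken it. The only stated look comes late, and a half-way O'Brien-Fleming boundary is very strict for a rare event in fewer than 40 participants per arm. A reader who sees suicide listed could believe that the rule guards against an imbalance when it does not.

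**Working it through.** **Inputs from the Protocol article.** Planned total 150, allocation 1:1, "alpha error = 0.05, beta error = 0.2", one interim look at half the participants (75, so about 37 versus 38; information fraction 0.5), registration 1 March 2011 to 30 September 2012. The article gives no suicide rate, so the risks below are assumptions shown as a range.

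**Reproducing the plan's own figure.** For effect size d, n per arm = 2(z_α + z_β)²/d². With d = 0.46 and two-sided 0.05: 2(1.960 + 0.842)²/0.46² = 74.2, so 75 per arm and 150 in total, as stated (152 by noncentral t). The stated 96 for d = 0.58 also fits a two-sided test. The stated 370 for d = 0.26 is close only to a one-sided test (366 to 368, against 466 to 468 two-sided). Sidedness is therefore not settled, and both versions are shown.

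**Timing.** Registration lasts 19 months. With even accrual half are enrolled at 9.5 months, and 9.5 + 18 = 27.5 months after the start. Enrolment closed at month 19.

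**Boundary.** For two equally spaced looks, find c so that P(|Z1| ≥ c√2 or |Z2| ≥ c) = 0.05, with correlation √0.5. This gives c = 1.977 and an interim boundary of 1.977 × √2 = 2.797, nominal two-sided p = 0.00517. With overall one-sided 0.05 the interim boundary is z = 2.373.

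**Suicides needed against zero in the other arm.** Pooled z = (y/n2 − x/n1)/√[p(1 − p)(1/n1 + 1/n2)], with p = (x + y)/(n1 + n2).

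- 0/37 versus 7/38: z = 2.742, does not cross.
- 0/37 versus 8/38: p = 8/75 = 0.1067, z = 0.2105/0.0713 = 2.953, crosses. Fisher's exact p = 0.00519, which just misses 0.00517.
- 0/37 versus 9/38: Fisher's exact p = 0.0023, crosses.
- Events in the 37-patient arm: pooled z crosses at 7 (2.816), Fisher at 8 (p = 0.0023).
- One-sided 0.05, events in the 38-patient arm: 6 by pooled z (2.520), 7 by Fisher.

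The two-sided counts are 7/37 = 19% to 9/38 = 24% of one arm; the loosest one-sided count is 6/38 = 16%. One suicide in the 37-patient arm raises the two-sided requirement in the other to 10 (pooled z) or 11 (Fisher).

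**Chance of crossing, 0% in the 37-patient arm and the assumed 18-month risk in the 38-patient arm:**

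| Assumed risk | Two-sided, pooled z | Two-sided, Fisher | One-sided, pooled z |
|---|---|---|---|
| 1% | 4 × 10⁻⁹ | 1 × 10⁻¹⁰ | 2 × 10⁻⁶ |
| 2% | 7 × 10⁻⁷ | 5 × 10⁻⁸ | 1 × 10⁻⁴ |
| 3% | 1 × 10⁻⁵ | 1 × 10⁻⁶ | 9 × 10⁻⁴ |
| 5% | 5 × 10⁻⁴ | 8 × 10⁻⁵ | 0.011 |
| 10% | 0.032 | 0.011 | 0.17 |

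If the events fall in the 37-patient arm instead, where pooled z needs only 7, P(X ≥ 7 of 37) at 5% is 0.002.

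**Self-harm, for contrast.** At assumed rates of 5% versus 30%, the chance of crossing is 0.54 (pooled z) or 0.45 (Fisher); at 5% versus 20% it is 0.16 or 0.10. Self-harm is not out of reach of the boundary. The limit there is direction: only a difference in favour of CAP is stated to count.

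**The case against.** The strongest reply is that this is a condensed article. The stopping rules are still to be planned, separate safety oversight may sit in a full protocol, inquiry sheets are assessed at every site, and each site's ethics committee is named. This stands as far as it goes. A reader might infer that participants have no protection against harm, and the article does not support that. What it does state is the direction of the trigger and the action on halting, and both point to benefit only. Weighing baseline data, missing data and site does not add a harm direction.

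Four other stronger readings also fail:

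- **That the prescribing component shows CAP to be hazardous.** The teams will "propose treatment and prescription strategies to psychiatrists according to the guidelines to eliminate unnecessary prescriptions". These are guideline-based proposals aimed at unnecessary prescriptions and are not evidence of risk.
- **That the cited longer-term results after EIS ends show harm.** The article describes loss of effectiveness, and it plans a transition strategy in response.
- **That self-harm cannot reach the boundary either.** The figures above show that it can.
- **That only GAF-F should stay in the rule.** Nothing here argues against re-admission or loss to follow-up as efficacy outcomes.

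The suicide risks are assumed and the sidedness is unstated. One-sided 0.05 lowers the count to 6 or 7, which is still about 16% to 18% of the 38-patient arm.

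**Conclusion.** The point holds in a limited form. The stated rule puts suicide and self-harm/suicide attempt under a trigger for CAP benefit, at one look about 27 months in if accrual is even, so an excess in CAP cannot set it off.

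For suicide the boundary is also practically unreachable in either direction, meaning a negligible probability and not an impossibility. Two-sided, it takes 7 to 9 suicides against none. At assumed risks up to 5% in one arm and 0% in the other, the chance is about 5 × 10⁻⁴ or less with events in the 38-patient arm, and 0.002 on the most favourable split and test. One-sided it is about 0.01 at 5%. At 10% crossing becomes possible but remains uncommon. The arithmetic does not extend to self-harm, and the finding does not say that safety oversight is absent from the trial.

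**What to change.** In the interim-analysis paragraph under Sample size:

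1. Stop treating suicide and serious self-harm as benefit-only outcomes. State that an imbalance against CAP at the interim look also prompts consideration of stopping the trial.
2. State that giving EIS to all participants on halting applies only to a benefit stop.
3. Tabulate suicides and severe self-harm by arm periodically from the inquiry sheets. Someone independent of the CAP teams and of the blinded raters should review the table, with a prespecified imbalance that prompts review in place of an O'Brien-Fleming p-value.

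If the full protocol already provides such monitoring, reconcile this paragraph with it and refer to it. The cost is a protocol amendment and a periodic table of reports that are collected anyway. The small downside is that one independent person sees unblinded counts.
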